##### Processing speed - Symbol Search Test

To examine processing speed abilities, two tasks will be used. First, the Symbol Search subtest of the WAIS-IV will require participants to quickly identify symbols that match one of two target symbols. This test is considered the most pure processing speed test available [65].

##### Processing speed - Color Naming Task

In addition, the Color Naming condition of the Color-Word Interference Test on the Delis-Kaplan Executive Function System (D-KEFS) [89] will be administered. This task requires participants to name the color of patches of ink across a page (red, blue, or green) as quickly as possible. This task has a low working memory loading and provides a measure of verbal processing speed [90].

##### Inhibitory control and set shifting - Color-word Interference Test

To examine executive functions (EFs), two full subtests of the D-KEFS will be administered. First, the Color-word Interference Test (CWIT) from the D-KEFS [89], which is based on the classic Stroop test, will be used as a measure of inhibitory control and set-shifting abilities. One condition of this test requires participants to name the color of the ink in which the words are printed while inhibiting the more salient response of reading the word. In another condition, participants are asked to switch between naming the color of the ink in which words are printed and reading the word aloud while not naming the ink color.

##### Cognitive flexibility - Trail Making Test

Another EF, cognitive flexibility, will be examined with the Number-Letter Switching Condition of the Trail Making Test [89]. In this visual-motor sequencing task, participants are required to alternate between connecting numbers and letters in ascending order.

##### Fluid intelligence - Raven’s standard progressive matrices

The Raven’s Standard Progressive Matrices [91] will be used as a measure of fluid intelligence. The test will be split into parallel even and odd forms of 30 items each and will be administered in a counterbalanced fashion across participants at pre- and post-training. In this task, participants are presented with a matrix of figures where one of the figures is empty. Through deducing the relationships between columns and rows, the participant is required to infer which figure should be placed in the empty position from six possible response options. The Raven’s test has been used to demonstrate gains in fluid intelligence following working memory training [31]. It is also one of the most widely used measures of fluid intelligence.

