**Fig. 1 Fig1:**
[figure not shown]
Participant flow through study. This figure illustrates participant enrollment, allocation, and follow-up throughout the study

All participants who meet the inclusion criteria will be randomly assigned to one of three conditions: (1) a working memory-training condition (27 participants), (2) a processing speed-training condition (27 participants), or (3) a no-training control condition (27 participants). Participants in the two training conditions will be blind to the fact that there are multiple training groups and to which cognitive domain they have been assigned to (that is, no mention of “working memory” or “processing speed” will be made). Group assignment will be determined by a Microsoft Excel randomization generator (that is, computer-generated random numbers). The random allocation sequence will be generated by a trained research assistant. Randomization will be performed as complete randomization with a 1:1:1 allocation. The allocation sequence will be concealed in sealed envelopes until the end of the pre-training assessment. A trained research assistant will also assign participants to interventions. Participants who are randomly assigned to the no training control condition will be given the opportunity to access the cognitive training games after their post-assessments. All researchers administering pre- and post-assessments will be blind to the group assignments of each participant.

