##### Fluid intelligence – Cattell’s Culture Fair Test

The Cattell’s Culture Fair Test (CCFT) Scale 3 will also be used as a measure of fluid intelligence [92]. Forms A and B will be administered in a counter-balanced fashion across participants at pre- and post-test. CCFT Scale 3 contains four subtests, including series, classifications, matrices, and conditions. The CCFT is considered a more comprehensive measure of fluid intelligence than matrix only tasks [93].

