### Procedure

In the first session, following informed consent (consent form provided in Additional file 3), demographic information will be collected and the Vocabulary and Matrix Reasoning subtests of the WASI-II will be administered by trained graduate students. Next, the trained students will interview participants with the SCID-5. Finally, the PANSS will be administered. The entire first session should last approximately 3 hours and 35 minutes.

The second session will include pre-assessment of all neurocognitive, social cognitive, and functioning measures described above. This session will be approximately 2 hours and 45 minutes in duration. To reduce the impact of fatigue and carryover effects on the results, the administration order of all cognitive and functional measures will be counter-balanced using a Williams Design Latin Square [104]. Testing will be administered by trained graduate students and research assistants, who will be blind to the randomization until completion of the baseline assessment. Blinding will only be broken if knowledge of the patient’s treatment group is necessary for further patient management. Following the baseline assessment, participants will be randomized and provided with training instructions, including how to access the online training in addition to the training schedule. Training program names (for example, *Bubble Math*, *Moving Memory*) will not be concealed; however, participants will not be informed of the objectives or hypotheses of the current study, and will be unaware of the other training conditions. Participants will be contacted half way through training (after approximately 5 weeks) to complete the mid-point motivation questionnaire.

The 3 hour 30 minute post-training assessment will be composed of the same measures (that is, neurocognitive measures, social cognitive measures, and measures of functional status) described above and using parallel forms where indicated, in addition to a re-administration of the PANSS. All post-assessments will be conducted by trained graduate students and research assistants who are blind to the randomization of each participant. All assessment materials will be scripted to ensure consistency across examiners and across assessments.

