### Statistical analysis

The following demographic variables at screening will be summarized: ethnicity, sex, age, and education. Between-group analyses of variance (ANOVAs) and chi square analyses will be used to examine any baseline differences between groups in demographics, individual characteristics (for example, sleep), cognition, and/or functioning. Any baseline differences will be corrected in all further analyses as appropriate.

Next, a three-group (working memory training, processing speed training, or no training) x time (pre-training or post-training) repeated measures ANOVA will be conducted to test for significant group differences in each domain of neurocognition (that is, memory, processing speed, executive functioning, and fluid intelligence) over time. Follow-up one-way repeated measures ANOVAs will be conducted as necessary to further examine the main effects of time. Follow-up independent *t*-tests will be conducted to examine differences in training- related gains between each training group and the no-training control group, based on the above-described *a priori* study objectives. Cohen’s *d* effect sizes will be reported. Notably, composite measures will be used where applicable (for example, a working memory composite, a processing speed composite).

Similarly, a group x time repeated measures ANOVA will be conducted to test for significant group differences in each social cognition task and each measure of daily functioning, with follow-up one-way repeated measures ANOVAs to follow-up on main effects of time and independent *t*-tests to examine group differences. Again, Cohen’s *d* effect sizes will be reported.

Finally, exploratory simple regression analyses will be conducted to examine potential moderating factors of training-related change. For any aspects of cognition and functioning that show significant training-related gains, regression analyses will be conducted using individual difference variables (for example, medication usage, sleep quality, duration of illness, intrinsic motivation) as the independent variable and change scores for each cognitive or functional domain as the dependent variable.

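### Form order on Raven's and Cattell's tests is counterbalanced but left out of the stated model, so any difference in form difficulty stays in the error variance of the primary fluid intelligence change (precision only)

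*Protocol article*

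**What the plan says.** Fluid intelligence is a primary outcome for both training arms. It is measured by two tests, each with a different form before and after training. For Raven's, "The test will be split into parallel even and odd forms of 30 items each", and these "will be administered in a counterbalanced fashion across participants at pre- and post-training". For Cattell's, "Forms A and B will be administered in a counter-balanced fashion across participants at pre- and post-test".

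The first form is taken before the arm is assigned. Under Recruitment process and study population, "The allocation sequence will be concealed in sealed envelopes until the end of the pre-training assessment". Under Procedure, "Following the baseline assessment, participants will be randomized and provided with training instructions". The allocation method is plain: "Randomization will be performed as complete randomization with a 1:1:1 allocation", with no stratification factor named.

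The Statistical analysis section specifies a three-group by two-time model: a "repeated measures ANOVA will be conducted to test for significant group differences in each domain of neurocognition". Independent t-tests then follow "to examine differences in training- related gains between each training group and the no-training control group". Composites are to be used where applicable, and the Discussion names a fluid intelligence composite as primary for both training groups. Form and form order do not appear in the description of the model.

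**The concern.** The design introduces a factor, which form comes first, and the stated analysis then does not use it. Suppose one half of Raven's is harder than the other. Patients who take the easier half first have their change pushed down, and patients who take it second have theirs pushed up. Averaged over patients the two shifts cancel, which is the purpose of counterbalancing. They do not cancel within a patient, so they widen the spread of change scores, and that spread is the yardstick for the group by time test and the t-tests on gains.

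At stake is sensitivity for far transfer to fluid intelligence, where the article's own background describes mixed and disputed findings and where there are only 27 patients per arm.

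**Working it through.** **Plan's own figure.** There is none to reproduce: the article states no difference between forms for either test and no pre-post correlation. Both are assumed below.

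**Inputs from the article.** Two forms per test, swapped between pre and post. Randomization after the pre-test. Arms of 27 (81 in total). d = .70 and alpha .05 (Recruitment process and study population).

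**Inputs assumed.** Pre-post correlation r = .7 among patients with the same form order. Forms differ by δ = 0, .2, .3 or .5 SD of the test score. Half the patients have each order.

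**Step 1: error variance.** With two time points, the group by time test is a one-way comparison of change scores, so the variance of change is what matters. In test-score SD units it is 2(1 − r) = 2 × .3 = .60. A shift of +δ for half the patients and −δ for the other half adds δ².

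| δ (test-score SD) | δ² / .60 | Rise in variance of change | Rise in its SD |
|---|---|---|---|
| 0 | 0 | 0% | 0% |
| .2 | .04 / .60 | 7% | 3% |
| .3 | .09 / .60 | 15% | 7% |
| .5 | .25 / .60 | 42% | 19% |

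The result depends on r. At r = .5 the denominator is 1.00 and the rises for δ = .2, .3 and .5 are 4%, 9% and 25%. At r = .8 it is .40 and they are 10%, 22.5% and 62.5%.

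**Step 2: power.** Read d = .70 in SDs of change within one form order. The effective d is then .70 / √(1 + δ²/.60), which is .70, .678, .653 and .588 for the four values of δ. A two-sided t-test with 27 per arm has power .714, .686, .653 and .564. The variance rise is equivalent to losing 1 − 1/(1 + δ²/.60) of the patients: 6%, 13% and 29% for δ = .2, .3 and .5.

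**Step 3: what a form-order term recovers.** A simulation with 27 per arm and 15,000 runs per setting used form differences of .2 and .5 SD of the change score. (At r = .7, test-score differences of .2, .3 and .5 correspond to .26, .39 and .65 SD of change.) Without the term, power was .70 and .62. With it, power was about .71 in both settings, the value expected with no form difference.

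**Step 4: validity.** In the same simulation with no treatment effect and no form-order term, type I error was .053 and .048, which is about 5%.

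**Step 5: chance imbalance.** Between two arms of 27, the share of patients on one order differs with SD √(2 × .25/27) = .136. At δ = .2 this moves the difference in mean change with SD 2 × .2 × .136 = .054. The standard error without a form effect is √(2 × .60/27) = .211, and √(.211² + .054²) = .218, the same 3% rise as in the table. Imbalance is therefore the route by which the added variance reaches the comparison, not an extra cost.

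**Step 6: the composite.** Take the average of two standardized tests with uncorrelated changes, each with variance .60. Its change variance is (.60 + .60)/4 = .30. If the two form orders are independent, the forms add 2δ²/4 = δ²/2, so the percentage rise is as for one test. If both tests share one order and the shifts point the same way, the forms add δ² and the rise doubles. If the shifts point opposite ways, they cancel. Positively correlated changes make the rise smaller. The article does not say whether the orders are linked or how the composite is scored.

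**The case against.** The strongest reply is that nothing here is an error. Randomization makes form order independent of arm, so the comparison is valid without the term. Counterbalancing does its main job, keeping form difficulty out of the time effect. The Raven's halves are described as parallel, so the difference may be near zero. A condensed article commonly leaves nuisance factors and scoring rules to the statistical analysis plan, and scoring standardized within form would largely remove the shift. All of this stands, and it limits the point to precision.

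The Statistical analysis section also promises correction for baseline differences. That does not replace a form-order term. It depends on a difference being found, and adjusting for the baseline score removes little of the shift. A patient with the easier form first gains δ/2 at pre and loses δ/2 at post. With a baseline slope of .7, the adjusted score still carries δ/2 + .7 × δ/2 = .85δ, against δ in the plain gain.

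Four stronger readings are tempting and are not supported:

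- A reader might infer bias or an inflated false-positive rate. Steps 4 and 5 show neither.
- A reader might count chance imbalance between arms as a second harm. It is already in the standard error.
- A reader might conclude that counterbalancing without a form term loses most of its value. It still separates form from time, which also protects the planned follow-up tests of time effects in expectation.
- A reader might take it as shown that form order is unbalanced within arms. The article does not describe the counterbalancing method, and a list prepared against the sealed sequence is possible, though not mentioned. Balance within arms would not help precision by itself, because without the term the shift would still be counted in the error variance.

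**Conclusion.** The point holds as a free improvement in precision, not as a flaw in validity. As stated, the model leaves any difference in form difficulty in the error variance of the primary fluid intelligence change. For a single test at r = .7, the cost is 0% of the variance of change if the forms are truly parallel, 7% at .2 SD, 15% at .3 SD and 42% at .5 SD. In power terms this runs from no loss to 15 points (.714 to .564), with the lower part of the range more in keeping with forms called parallel. These figures rest on the assumed correlation, the assumed form difference and an even split of orders. That the final analysis omits form order is not established, because only the article is available.

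**What to change.** Record which form each patient took first, separately for Raven's and Cattell's. In the analysis plan, add form order to the models for Raven's, Cattell's and the fluid intelligence composite: as form order by time in the repeated measures model, or as a fixed factor where gain or post-training scores are compared. For the composite, include the order for each test unless the two are linked. Label the term as there for precision only.

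The cost is about one degree of freedom per test and one recorded item per test, with no added burden on patients. Assigning orders by alternating study numbers would not balance them within arms under complete randomization and is not needed, since the model term does the work.

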##### Fluid intelligence – Cattell’s Culture Fair Test

The Cattell’s Culture Fair Test (CCFT) Scale 3 will also be used as a measure of fluid intelligence [92]. Forms A and B will be administered in a counter-balanced fashion across participants at pre- and post-test. CCFT Scale 3 contains four subtests, including series, classifications, matrices, and conditions. The CCFT is considered a more comprehensive measure of fluid intelligence than matrix only tasks [93].

#### Social cognitive measures

Social cognitive measures will examine emotion recognition and theory of mind abilities.

##### Emotion recognition - Geneva Emotion Recognition Test

First, the Geneva Emotion Recognition Test will be used to examine emotion recognition abilities using face, voice, and body cues. This test includes 83 short video clips with sound, with 10 actors portraying 14 different emotions. Following each clip, participants are asked to choose which of 14 emotions the actor was trying to portray [94]. Importantly, this task also requires timely information processing due to the brief nature of the clips.

##### Theory of mind - Hinting Task

Finally, the Hinting Task, one of the few consistently utilized theory of mind measures in the schizophrenia literature, will be administered. This task requires participants to listen to a verbally presented story and identify the intention of one character when he or she provides a verbal hint to a second character. The 10 items from the original Hinting Task [95], as well as the 10 more recently developed scenarios [96] will be utilized, with five questions from each set being randomly selected and administered at pre-assessment, and the other five questions from each set administered at post-assessment.

#### Beliefs regarding cognition

The *Need for Cognition Scale* and the *Theories of Intelligence Scale* will be used to examine participants’ beliefs regarding cognition.

##### Need for cognition scale

The short form of the Need for Cognition Scale [97] will be used to examine how much participants enjoy cognitively stimulating or challenging tasks. Responses to this questionnaire are provided on a 5-point Likert scale with 18 questions in total.

##### Theories of Intelligence Scale

The Theories of Intelligence Scale is an eight-item scale that will be used to examine the degree to which participants believe that cognitive abilities (that is, intelligence) are fixed or malleable [98]. Responses to this questionnaire are provided on a 6-point Likert scale.

#### Measures of functional status

Cognitive, social, and occupational functioning in daily life will be examined.

##### Functioning - Cognitive Failures Questionnaire

The Cognitive Failures Questionnaire (CFQ) will assess an individual’s proneness to cognitive errors and slips while completing everyday tasks. This measure has been successfully utilized with schizophrenia patients to examine perception, memory, and motor lapses in daily life [99].

##### Functioning - UCSD Performance-based Skills Assessment - Brief

The UCSD Performance-Based Skills Assessment (UPSA-Brief) [100] will be used to assess functional capacity in schizophrenia patients. This role-play test will be used to assess performance in two basic living skills: finance and communication.

##### Functioning – social and occupational functioning assessment scale

In addition, the Social and Occupational Functioning Assessment Scale (SOFAS) [101] will be used to assess social and occupational functioning using a clinician-rated scale between 1 and 100.

#### Questionnaires

Two questionnaires, related to sleep and motivation, will be administered to each participant.

##### Brief sleep questionnaire

Given that sleep quality has been associated with cognitive functioning, a brief measure will be administered. All patients will be asked the following questions based on the previous month: 1) What time do they usually go to bed? 2) How long does it usually take them to fall asleep? 3) What time do they usually wake up? and 4) How many hours of actual sleep do they usually obtain each day? These questions were adapted from the Pittsburgh Sleep Quality Questionnaire [102].

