### Objectives and hypotheses

This study will investigate 1) near-transfer gains associated with working memory and processing speed training in schizophrenia patients (that is, gains in the working memory or processing speed domains, respectively); 2) far-transfer gains associated with working memory and processing speed training in schizophrenia patients (that is, gains in other neurocognitive domains, primarily fluid intelligence, and gains in social cognition); and 3) real-world gains associated with working memory and processing speed training in schizophrenia patients (that is, gains in daily functioning). In addition, exploratory analyses will examine the effect of individual difference variables (that is, sleep quality and intrinsic motivation) on training-related gains. The primary outcome measures are as follows: working memory, processing speed, and fluid intelligence.

The corresponding hypotheses are as follows: 1) post-training performance in working memory and processing speed will improve in the working memory training group and processing speed training group, respectively, relative to the no-training control group (that is, both training groups will show near transfer in their own domain); 2) both working memory and processing speed training will lead to more generalized improvements in other neurocognitive domains, particularly fluid intelligence, compared to the no-training control group, as well as enhancements in social cognition relative to the no-training control group; and 3) both working memory and processing speed training will lead to more improvements in daily functioning compared to the no-training control group. Given the current paucity of research comparing the gains associated with specific training programs, no hypotheses are made with regards to which training group (that is, working memory or processing speed) will show greater improvements in neurocognition, social cognition, or daily functioning. Rather, comparisons between training groups will be exploratory in nature.

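### The four sleep questions measure timing, latency and total daily duration, not the sleep quality that the exploratory moderator analysis names

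*Protocol article*

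**What the plan says.** Under Objectives and hypotheses, the protocol article states that "exploratory analyses will examine the effect of individual difference variables (that is, sleep quality and intrinsic motivation) on training-related gains". Under Statistical analysis, the regressions on change scores are described as "using individual difference variables (for example, medication usage, sleep quality, duration of illness, intrinsic motivation) as the independent variable".

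The instrument is set out under Brief sleep questionnaire. Its rationale is the same construct: "Given that sleep quality has been associated with cognitive functioning, a brief measure will be administered". Four questions about the previous month follow. They cover bedtime ("What time do they usually go to bed"), the time taken to fall asleep, waking ("What time do they usually wake up") and duration ("How many hours of actual sleep do they usually obtain each day"). The article says that they are adapted from a longer sleep-quality instrument.

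Table 1 lists no other sleep measure. It gives this questionnaire no primary or secondary outcome status and allots 5 minutes to it before and after training. Statistical analysis also names sleep as an example of an individual characteristic to be compared between groups at baseline, and says that baseline differences will be corrected for in later analyses as appropriate. The article nowhere defines a sleep score or a sleep efficiency.

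**The concern.** The planned variable and the instrument do not match. Objectives and hypotheses names only two individual-difference variables, and sleep quality is one of them. The questions fixed for it record clock times and durations. A patient who sleeps 7.5 hours restlessly and one who sleeps 7.5 hours soundly, with the same bedtime, latency and wake time, give identical answers. A scoring rule in the full protocol or SAP could combine the four answers, but it could not separate these two patients.

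There is a second, smaller problem of reference period. The first three items describe one main sleep period; the fourth asks about the day. A respondent who naps may reasonably include the naps. The duration variable then mixes night sleep with daytime sleep, and daytime sleep may be a response to a poor night.

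At stake is the interpretation of the sleep moderator. A null regression could not be read as showing that sleep quality does not matter, and a positive one could not be attributed to quality. The sleep data could also enter the main analyses, if a baseline imbalance in sleep were found and adjusted for.

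**Working it through.** The article gives no sleep figure to reproduce. The check has two parts: a comparison of items with the construct, and arithmetic on assumed answers.

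**1. What each item supplies**

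| Item | Supplies | Does not supply |
|---|---|---|
| 1 Bedtime | timing | quality |
| 2 Time to fall asleep | latency, a partial indicator of quality | night waking, disturbance |
| 3 Wake-up time | timing | time of getting out of bed |
| 4 Hours of actual sleep per day | total daily duration | the split between night and daytime sleep |

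No row supplies a rating of quality, night waking or disturbance.

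**2. Effect of counting naps on duration (assumed values)**

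Let W be the hours from bedtime to waking, L the latency, A the time awake during the night and N the daytime sleep. Then:

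- night sleep = W − L − A
- item 4, if naps are counted = W − L − A + N

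Take two patients, both in bed at 23:00 and awake at 07:00, so W = 8 h.

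- First patient: L = 0.25, A = 0, N = 0. Night sleep 7.75 h; item 4 is 7.75 h.
- Second patient: night sleep 7 h (L + A = 1), N = 2. Item 4 is 7 + 2 = 9 h.

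The second patient has the shorter night but the longer recorded duration. For this pair the order reverses once the nap exceeds 7.75 − 7 = 0.75 h. With no nap, or with item 4 read as night sleep, the order is kept.

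**3. Effect on a sleep efficiency, if one were derived**

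The article does not plan this ratio; it is shown only because the items would permit it.

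Ratio = item 4 / W = 1 + (N − L − A)/W. It exceeds 100% only when N > L + A.

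| Bed–wake | L (h) | A (h) | N (h) | Ratio with nap counted | Night only |
|---|---|---|---|---|---|
| 23:00–07:00 | 0.5 | 0 | 0 | 7.5/8 = 93.75% | 93.75% |
| 23:00–07:00 | 0.5 | 0 | 0.5 | 8/8 = 100% | 93.75% |
| 23:00–07:00 | 0.5 | 0 | 1 | 8.5/8 = 106.25% | 93.75% |
| 23:00–07:00 | 0.5 | 0 | 2 | 9.5/8 = 118.75% | 93.75% |
| 23:00–07:00 | 0.5 | 1 | 1 | 7.5/8 = 93.75% | 6.5/8 = 81.25% |
| 01:00–07:00 | 0.25 | 0 | 1 | 6.75/6 = 112.5% | 5.75/6 = 95.8% |

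In the fifth row the nap cancels an hour awake at night: the ratio equals that of the first row, so the masking occurs below 100% as well.

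**4. Wake-up time on its own**

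Assume bed at 23:00, waking at 07:00, getting up at 08:30, 7 h of night sleep and no nap. Over time in bed the efficiency is 7/9.5 = 73.7%. Up to waking it is 7/8 = 87.5%. Using wake-up time raises the ratio but does not take it past 100%. With coherent answers, only daytime sleep does that.

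**The case against.** The strongest reply is that a brief proxy is a defensible choice in a session of 2 hours 45 minutes, and that latency and duration do carry information about quality. That stands. A reader might infer that the four items cannot yield any sleep-quality variable, or that the exploratory question cannot be answered at all. The document does not support this, because latency is asked directly and duration is available as a second indicator. What is out of reach is a rated or disturbance-based measure.

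A reader might also infer that the trial will compute an efficiency above 100% and rank napping patients as the best sleepers. That goes too far. No efficiency is planned, the absence of a scoring rule from the article is not a fault, and nothing in the document shows how often these patients nap.

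The nap effect further depends on how respondents read item 4. Coming after three questions about the main sleep period, it may be answered for the night alone. The questions are printed in the third person, and Procedure says that assessment materials will be scripted, so the words put to patients may differ. This makes the nap point conditional. It leaves the main point intact, since no wording of these four items asks about quality.

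Finally, the baseline comparison refers only to sleep, which the items fit, and the regressions are run only for outcomes that show significant gains. Both limit the consequence.

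**Conclusion.** The point holds as a mismatch of name and content. The instrument measures sleep latency, duration and timing; the plan calls the resulting moderator sleep quality. This follows from the text and needs no assumption beyond the item content as printed.

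The masking of poor night sleep by naps is a possibility, not a demonstrated error. It rests on respondents counting daytime sleep in item 4 and on the assumed sleep times above. Under those values a nap longer than 45 minutes is enough to reverse two patients whose night sleep differs by that amount.

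The importance is low. No primary or secondary outcome and no part of the sample size depends on the questionnaire. The one route to the main analyses is adjustment for a baseline imbalance in sleep, should one arise.

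**What to change.** Trial status says that recruitment has not begun, so the questionnaire can still be changed.

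- Add one item asking for an overall rating of sleep quality over the past month, and use it as the sleep-quality variable, with latency and duration in support.
- Word item 4 as hours of sleep at night. If daytime sleep is of interest, ask about naps separately.
- Ask the time of getting out of bed only if a sleep efficiency will be derived.

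If the questionnaire is to stay as it is, name the variable sleep latency, duration and timing under Objectives and hypotheses and under Statistical analysis, and limit the conclusion to that. If the scripted wording already restricts item 4 to the night, the second change is unnecessary.

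The added items cost about one minute at each assessment, against the 5 minutes that Table 1 allots. Renaming costs nothing in patient time, but gives up the claim about quality.
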